### Description of statistical methods

#### Sample size calculation

Systematic reviews have revealed that the rate of disease recurrence after ART is 3.8 to 4.7% [10, 19]. The 5-year DFS of ART in a Chinese study was 96.5% [20]. In our study, we assume that the recurrent rate of ART of 5 years is 5%. A noninferiority log-rank test with an overall sample size of 331 subjects (165 in the reference group and 166 in the treatment group) achieves 90.1% power at a 0.050 significance level to detect an equivalence hazard ratio of 0.75 when the actual hazard ratio is an equivalence hazard ratio of 1.00, and recurrence rates of 5 years in the MIRT and ART group are 7 and 5% [21]. Considering the possible 20% rate of loss to follow-up, 414 patients are needed to accomplish the study goal.

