**Methods:**

This is a noninferiority, randomized controlled trial performed at 28 Chinese centers; the study is designed to compare the oncologic and fertility outcomes of patients treated by MIRT (robot-assisted or laparoscopic RT) or ART. Patients will be recruited if they have been diagnosed with stage IA1 (with lymphovascular space invasion), IA2, or IB1 CC (with a maximum tumor diameter ≤ 2 cm) in the FIGO 2009 staging system and histological subtypes of squamous carcinoma, adenocarcinoma, or adenosquamous carcinoma and if they are also aged 18 to 40 years. These candidates will be randomly assigned to undergo MIRT or ART. The primary endpoint will be disease-free survival. Secondary endpoints will consist of overall and disease-free survival rates, fertility outcomes, and quality of life. A total of 414 patients are needed to accomplish the study goal, with 90.1% power at a 0.050 significance level to detect an equivalence hazard ratio of 0.75 in the ART group, considering 20% loss to follow-up.

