#### Statistics

Continuous variables conformed to the normal distribution will be described with means and standard deviations, and discrete variables not conformed to the normal distribution will be summarized with medians, ranges, and interquartile ranges. The *t* test will be used for continuous variables, and the chi-square test or Fisher’s exact test will be used for categorical variables. To evaluate the strength of associations, bivariate and multivariable logistic regression analyses will be used, and the strength of associations will be expressed as hazard ratios (HR) with 95% confidence intervals (95% CI). Kaplan-Meier plots will be generated for recurrence and death rates between the groups, and the log-rank test will be applied for the eventual significant differences. The survival outcomes will be compared according to intention to treat and per protocol. The analysis of intention to treat is available for protocol nonadherence. These statistical analyses will be performed using SPSS 22.0 (SPSS Inc., Chicago, IL, USA). All analyses will be two-sided, and significance will be set at a *P* value of 0.05.

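### The stated 90.1% power cannot be reproduced: the 0.75 margin needs about 416 recurrences at one-sided 0.05, the stated rates give about 17 to 21, and power is then about 15%

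*Protocol article*

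**What the plan says.** All design inputs are in the protocol article, under Sample size calculation.

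- **Test and size:** "A noninferiority log-rank test with an overall sample size of 331 subjects (165 in the reference group and 166 in the treatment group").
- **Power, alpha, margin:** the test "achieves 90.1% power at a 0.050 significance level to detect an equivalence hazard ratio of 0.75 when the actual hazard ratio is" 1.00.
- **Control rate:** "In our study, we assume that the recurrent rate of ART of 5 years is 5" per cent. The power sentence itself then gives 5-year recurrence of 7% for MIRT and 5% for ART.
- **Loss:** 20%, which raises the total to 414.

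The Abstract (Methods) carries the same claim: "with 90.1% power at a 0.050 significance level to detect an equivalence hazard ratio of 0.75 in the ART group".

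The Sample size calculation does not say whether the 0.050 is one- or two-sided. The Statistics section does: "All analyses will be two-sided, and significance will be set at a" P value of 0.05. No required or expected number of events is given.

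**The concern.** The power of a log-rank test is driven by the number of events. With recurrence of about 5% over five years, a few hundred women produce around twenty events, while a hazard-ratio margin of 0.75 is narrow and needs several hundred. A claim of 90% power from these inputs looks wrong by more than an order of magnitude in events.

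This is the calculation that justifies the sample size for the primary endpoint of a noninferiority trial on oncologic safety. If it is wrong, two misreadings follow. Failure to show noninferiority could be taken as evidence against MIRT, although a trial this size would usually fail even if the two approaches were equivalent. Conversely, the Statistics section plans a log-rank test for differences. With about twenty events that test will usually be non-significant, and a reader who trusts the 90.1% may take this as showing that MIRT is no worse.

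**Working it through.** **Inputs (Sample size calculation unless noted).** Evaluable N = 331, about 1:1; total 414. Margin 0.75, taken as ART/MIRT and so 1.333 as MIRT/ART; |ln 0.75| = 0.2877 in either direction. True hazard ratio 1.00. ART 5-year recurrence 5%. Alpha 0.05, tried both as one-sided 0.05 and as one-sided 0.025 (the two-sided 0.05 of the Statistics section).

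**Step 1: the loss adjustment reproduces.** 331 / (1 − 0.20) = 413.75, rounded up to 414. The problem is not there.

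**Step 2: events needed for 90.1% power (Schoenfeld).** D = 4 (z_alpha + z_power)² / (ln 0.75)²

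- One-sided 0.05: 4 × (1.645 + 1.287)² / 0.2877² = 415.5, so 416. Freedman's formula gives 422.
- One-sided 0.025: 4 × (1.960 + 1.287)² / 0.2877² ≈ 510.

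**Step 3: events expected at 5% recurrence.** 331 × 0.05 = 16.6. For 414 women with no loss at all, 414 × 0.05 = 20.7.

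The shortfall at one-sided 0.05 is 416/20.7 ≈ 20-fold to 416/16.6 ≈ 25-fold. Reaching 416 events at 5% would take 416/0.05 = 8,320 evaluable women, or 8,320/0.8 = 10,400 enrolled.

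**Step 4: power at the expected events.** Power = Φ(0.2877 √D / 2 − z_alpha)

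| Scenario (true HR 1.00) | Events | One-sided 0.05 | One-sided 0.025 |
|---|---|---|---|
| 331 women, 5% in both arms | 16.6 | 14.5% | 8.5% |
| 414 women, no loss, 5% in both arms | 20.7 | 16.1% | 9.6% |
| 414 women, no loss, 7% in both arms | 29.0 | 19.2% | 11.8% |

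Replacing the log scale by a linear effect scale (1/0.75 − 1 = 0.333) raises the most favourable cell, the last row at one-sided 0.05, only to 22.7%. Simulating recurrence counts and applying the score test at the margin gives 13.5% (331 women) and 15.7% (414) at one-sided 0.05, and 8.4% and 9.5% at one-sided 0.025.

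**Step 5: the 7% and 5% rates taken literally.** Under proportional hazards they imply a hazard ratio of ln(0.93)/ln(0.95) = 1.41. That contradicts the true hazard ratio of 1.00 in the same sentence and lies beyond 1.333. At 331 × 0.06 = 19.9 events, power = Φ((√19.9 / 2) × (ln 1.333 − ln 1.415) − 1.645) = 3.8% at one-sided 0.05, and 1.8% at one-sided 0.025.

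**Step 6: the margin this size can test.** For 90% power at one-sided 0.05, margin = exp(2 × 2.926 / √D). This is 3.6 at 20.7 events and 4.2 at 16.6 events. With 5% ART recurrence, 1 − 0.95^3.62 = 16.9% and 1 − 0.95^4.22 = 19.4%, so the margin is about 12 to 14 percentage points.

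**The case against.** **A different formula, alpha or rate might rescue the figure.** None tried with the stated recurrence rates does; the best reaches about 23%. One-sided 0.05 is already the kinder reading of alpha.

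**The figure may be a data-entry slip.** On the linear effect scale at one-sided 0.05, 331 women give 90.0% to 90.2% if 93% to 94% of them are counted as events. That would fit survival proportions having been entered as event proportions. It is conjecture, and it would explain the error rather than support the power.

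**A reader might infer that 331 women could not give 90.1% power even if every one recurred.** The documents do not support this. It holds on the log hazard-ratio scale (83.5% with 331 events) but not on the linear scale (about 92%), and the protocol does not say which formula was used. What is supported is that 90.1% does not follow from the stated recurrence rates.

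**A reader might also take 15% as the power of the trial.** It is conditional on 5% in both arms and one-sided 0.05. The stated 7% against 5%, or the two-sided 0.05 of the Statistics section, gives less. The event count is also approximate: 21 assumes no loss, against the planned 20%, and Trial status starts the primary analysis in December 2023, before the last participant reaches five years in December 2025. These points move the answer by a few percentage points, not towards 90%.

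**A margin of 6 to 7 percentage points might look attainable.** It comes from a different test, the difference in 5-year proportions: 2.926 × √(2 × 0.05 × 0.95 / n) is 6.3 points at n = 207 per arm and 7.0 at n = 165.5. Those points correspond to hazard ratios of only about 2.3 to 2.5, not to 3.6 to 4.2.

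**Conclusion.** The point holds. The 90.1% power cannot be reproduced from the inputs printed beside it. At the 0.75 margin with a true hazard ratio of 1.00 and 5% recurrence in both arms, power is about 14.5% to 16.1% at one-sided 0.05, or 8.5% to 9.6% at one-sided 0.025. If the approaches are truly equivalent, noninferiority would be missed about 84% to 86% of the time on the first reading and about 90% to 92% on the second. The stated 7% and 5% cannot stand together with a hazard ratio of 1.00, and under them power is about 4% or less.

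This rests on 1:1 allocation, proportional hazards, events equal to N times the 5-year recurrence, and the 0.75 being the noninferiority margin. The size of the discrepancy does not hinge on which log-rank approximation is used.

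**What to change.** - Withdraw the 90.1% in the Abstract and in the Sample size calculation.
- Reconcile the 7% and 5% rates with the assumed true hazard ratio of 1.00.
- Keep N = 414. State the alpha and its sidedness for the noninferiority test, the direction of the 0.75 ratio, the expected events (about 17 to 21) and the actual power at that margin.
- If a detectable margin is quoted, say that 90% power at one-sided 0.05 supports only a hazard ratio of about 3.6 to 4.2, which is about 12 to 14 percentage points at 5% ART recurrence. Do not present 6 to 7 points as its equivalent.
- Limit the planned conclusion to an effect estimate with a confidence interval unless a margin that this size can test is justified on clinical grounds. Working back from N to a margin is not such a justification.
- State that a non-significant log-rank test will not be read as noninferiority.

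The cost is amendment wording and a much less favourable stated power. No extra patients are needed.

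### The power statement assumes both a true hazard ratio of 1.00 and 5-year recurrence of 7% against 5%; these are incompatible, the role of the 7% is undefined, and the 90.1% must be recomputed

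*Protocol article*

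**What the plan says.** All the planning inputs stand in the Sample size calculation section of the protocol article. For the open arm, "we assume that the recurrent rate of ART of 5 years is 5" per cent. The noninferiority log-rank test on 331 evaluable women (165 and 166) "achieves 90.1% power at a 0.050 significance level" and is meant "to detect an equivalence hazard ratio of 0.75". Two conditions are attached to that power. The first is that "the actual hazard ratio is an equivalence hazard ratio of 1.00". The second, joined to it by "and", is that the "recurrence rates of 5 years in the MIRT and ART group are 7 and 5" per cent. Allowing for 20% loss to follow-up brings the total to 414.

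The abstract repeats the margin and is the only place that hints at its direction: the trial is powered "to detect an equivalence hazard ratio of 0.75 in the ART group". The Statistics section adds: "All analyses will be two-sided, and significance will be set at a" P value of 0.05. The sample size section does not say whether its own 0.050 is one-sided or two-sided.

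**The concern.** Equal hazards mean equal 5-year recurrence. With ART at 5%, a true hazard ratio of 1.00 puts MIRT at 5%, not 7%. The power statement is therefore conditioned on two things that cannot both be true, and nothing else in the article reconciles them.

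This matters because the assumed truth and the margin are the two quantities that define a noninferiority design. A reader cannot tell whether 7% is what the investigators expect under MIRT or the worst they would tolerate. Someone writing or checking the analysis plan would have to guess, and the stated power cannot be verified on either guess.

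**Working it through.** **Inputs** (Sample size calculation, and the abstract for direction): ART 5%; MIRT 7%; true hazard ratio 1.00; margin 0.75, read as ART/MIRT, so 1/0.75 = 1.333 as MIRT/ART; 331 evaluable; about 1:1 allocation; alpha 0.05; power 90.1%; 20% loss.

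**1. The plan's own figures.** The inflation reproduces: 331/0.80 = 413.75, so 414. The 331 does not. The Schoenfeld formula for a true hazard ratio of 1.00 is

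events = 4 × (z_alpha + z_power)² / (ln 1.333)²

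- One-sided 0.05: 4 × (1.645 + 1.287)² / 0.2877² = 415.5, so 416 events.
- One-sided 0.025: 4 × (1.960 + 1.287)² / 0.2877² = 509.6, so 510 events.

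A variant that replaces ln 1.333 by (1.333 − 1) needs 309.5 events at one-sided 0.05. It returns 326 to 333 women only if 93% to 95% of them have an event. That would fit disease-free proportions having been entered as event proportions, but this is inference from the arithmetic and the article does not say it.

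**2. The hazard ratio implied by the rates.** Under proportional hazards:

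- ART/MIRT = ln(1 − 0.05)/ln(1 − 0.07) = 0.0513/0.0726 = 0.707; inverse 1.415.
- Rounding: 4.5–5.5% for ART and 6.5–7.5% for MIRT span ART/MIRT 0.59 to 0.84. None of these is 1.00.
- With ART held at 5%, MIRT at 6.5% gives 0.763, just inside the 0.75 margin.

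**3. The rate implied by the margin.** 1 − 0.95^(1/0.75) = 0.066. With ART at 5%, the margin is 6.6% in MIRT, a difference of 1.6 percentage points.

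**4. If 7% is the expected MIRT rate, at face value.** Events: 331 × 0.06 = 19.9.

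Chance of declaring noninferiority = Φ[(ln 1.333 − ln 1.415) × √19.9/2 − z]

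- One-sided 0.05: Φ(−0.132 − 1.645) = 3.8%.
- One-sided 0.025: Φ(−0.132 − 1.960) = 1.8%.

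**5. If the truth is 5% in both arms.** Events: 331 × 0.05 = 16.6.

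Power = Φ[ln 1.333 × √16.6/2 − z]

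- One-sided 0.05: Φ(0.585 − 1.645) = 14%.
- One-sided 0.025: Φ(0.585 − 1.960) = 8%.
- With all 414 women followed (20.7 events): 16% and 10%.
- Women needed for 90.1% power at 5% recurrence, one-sided 0.05: 415.5/0.05, about 8,310.

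**The case against.** The strongest defence is that the truth used for power is stated outright as 1.00, that nothing calls 7% the expected MIRT rate, and that 7% may simply be the rate at the margin: 6.6% rounded to a whole per cent. Much of this stands. It is a plausible reading, and on it the 3.8% does not apply and the defect is a missing label. It does not clear the sentence as written, which presents 7% as a MIRT group rate holding alongside a hazard ratio of 1.00.

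A reader might infer several stronger things that the article does not support:

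- *That the trial is designed to fail.* This follows only if 7% is the expected truth and is taken unrounded. A rate of 6.5% would also print as 7% and falls just inside the margin.
- *That the plan has two margins, 1.33 and 1.41.* The only stated margin is 0.75. The 1.41 is derived from the two rates and appears nowhere as a decision limit.
- *That the abstract and the sample size section disagree on direction.* They do not. The abstract attaches 0.75 to ART, and the sample size section gives no direction. ART/MIRT is also the only reading on which 0.75 is a noninferiority margin.
- *That deleting the 7% restores the 90.1%.* Step 5 of the working shows that it does not.

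**Conclusion.** The point holds in this form: the stated rates contradict the stated true hazard ratio, the role of the 7% is undefined, and the 90.1% power does not follow from the plan's inputs on either reading. The contradiction needs only proportional hazards and survives any rounding of the two rates. How 7% sits against the margin is less firm: at face value it is beyond 0.75, and within rounding it straddles it.

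The larger consequence is the power. With equal 5% recurrence, 331 women give about 17 events, about 4% of the 416 needed at one-sided 0.05 (17/416). The power figures rest on the Schoenfeld approximation, 1:1 allocation, and 5-year recurrence as the probability of an event. Because the sidedness of the sample size alpha is not stated, both levels are shown; the shortfall is large at either.

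**What to change.** In the Sample size calculation section and in the abstract, in the same words:

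1. State one assumed truth: 5-year recurrence of 5% in both arms, hazard ratio 1.00.
2. State the margin once with its direction: ART/MIRT 0.75, equivalently MIRT/ART 1.33, about 6.6% against 5% at 5 years.
3. Remove 7% as a planning rate, or label it as the rounded MIRT rate at the margin.
4. State whether the sample size alpha is one-sided 0.05 or 0.025, and reconcile it with the two-sided rule in the Statistics section.
5. Recompute and restate the power on those inputs, with the expected number of events.

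Items 1 to 4 cost an amendment of wording. Item 5 is quick to calculate, but its result cannot be absorbed as wording: it shows a shortfall of roughly 400 events, which the sponsor must either address in the design or acknowledge. If recruitment cannot grow, the plan should give the expected precision instead of 90.1% power. With 16.6 events and an observed hazard ratio of 1.00, the 95% interval is exp(±1.96 × 2/√16.6), about 0.38 to 2.62, against an upper limit of 1.33.

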#### Statistics

Continuous variables conformed to the normal distribution will be described with means and standard deviations, and discrete variables not conformed to the normal distribution will be summarized with medians, ranges, and interquartile ranges. The *t* test will be used for continuous variables, and the chi-square test or Fisher’s exact test will be used for categorical variables. To evaluate the strength of associations, bivariate and multivariable logistic regression analyses will be used, and the strength of associations will be expressed as hazard ratios (HR) with 95% confidence intervals (95% CI). Kaplan-Meier plots will be generated for recurrence and death rates between the groups, and the log-rank test will be applied for the eventual significant differences. The survival outcomes will be compared according to intention to treat and per protocol. The analysis of intention to treat is available for protocol nonadherence. These statistical analyses will be performed using SPSS 22.0 (SPSS Inc., Chicago, IL, USA). All analyses will be two-sided, and significance will be set at a *P* value of 0.05.

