### Secondary objectives and secondary endpoints

The secondary objectives are as follows:
To evaluate the OS at the 5-year follow-upTo assess different strategies of RT in terms of fertility and obstetric outcomesTo compare the incidence of perioperative complications of different surgical approachesTo compare major perioperative complications within 28 days after surgery and major postoperative complicationsTo determine the general and specific QoL

Secondary endpoints will therefore be the following:
All-cause mortalityFertility outcomes consisting of cervical incompetence, natural pregnancy, and infertility treatment such as intrauterine insemination or IVF-ET; obstetric outcomes consisting of the time interval between the RT surgery and pregnancy; the overall mean length of time during which conception was attempted; the number of pregnancies; the mode of delivery; and the outcome of each pregnancy, such as spontaneous abortion, induced abortion, drug abortion, preterm birth, premature rupture of membranes, fetal growth restriction, and full-term birthPerioperative complications consisting of injury of the ureter, bladder, bowel, blood vessels, or nerves, and vaginal bleeding, and postoperative complications consisting of postoperative pelvic infection, pelvic lymphocele, intrauterine infection, Asherman syndrome, abnormal menstruation, urinary tract infection, hydronephrosis, intestinal obstruction, chronic pain, varices at the site of uterovaginal anastomosis, and fistula formationMajor perioperative and postoperative complications consisting of early postoperative complications (cerebrovascular, pulmonary, and renal diseases; ileus; abdominal wound complications; septicemia; thromboembolism; and lymphocele formation and secondary infection) and delayed postoperative complications (lymphedema, vaginal evisceration)QoL assessment comprising the authorized Chinese edition of EORTC QLQ-C30 [13] and its CC module QLQ-CX24 [14], the 19-item Female Sexual Function Index (FSFI) [15], and the PFIQ-7 questionnaire [16].

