### Data management

All medical information required according to the protocol will be collected via the case report forms based on the website, facilitating the real-time, central assessment of the data completeness and patient follow-up. This information will include demographic data, the surgical approach, the skin-to-skin operative time, EBL, and the surgical energy devices. The pathogenic material will also be collected, including the results regarding the tumor histology subtype, FIGO stage, grade (well, moderately or poorly differentiated), tumor size, depth of stromal invasion, LVSI, lymph node status, and surgical margin status. After RT, data on surgical complications, bladder/intestinal function recovery, QoL, fertility and obstetrics outcomes, and disease recurrence and survival information will also be followed.

The questionnaires will be completed, the ovarian reserve function will be evaluated, and a urodynamic study (UDS) and anorectal manometry will be assessed within 4 weeks before surgery, at 4 months postoperatively, at 12 months postoperatively, and then once a year thereafter. After the RT (Table 1), the patients will be required to attend the customed follow-up regularly, at 3- to 6-month intervals in the first 2 years after completing the treatment, 6- to 12-month intervals from the third to the fifth year after treatment, and then at 1-year intervals thereafter. The effects of the follow-up scheme (pelvic examination, the ThinPrep cytological test and/or human papillomavirus testing, transvaginal ultrasonography, an abdominal ultrasound scan, chest radiography, and serum tumor marker, i.e., squamous cell carcinoma and Ca125) will be evaluated at each visit.

**Table 1 Tab1:** Lists of clinical assessments at different time points

Check-up time	Inspection items	Documentors	Directors
Within 4 weeks before RT	Urodynamic assessment	CRF	Research centers
	Anorectal manometry	CRF	
	QoL assessment	CRF	
	Sexual function scale	CRF	
	Ovarian reserve function	CRF	
Ten to 14 days after RT	Operation details	CRF	Research centers
	Residual urine	CRF	
	Perioperative complications	CRF	
Four weeks after RT	Postoperative complications	CRF	
	Pathological report	CRF	
Four months after RT	Urodynamic assessment	CRF	Research centers
	Anorectal manometry	CRF	
	QoL assessment	CRF	
	Ovarian reserve function	CRF	
	Postoperative adjuvant therapy	CRF	
	Data curation	Database	Main center
Every 12 months after RT	Urodynamic assessment	CRF	Research centers

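### The stated t test would compare time from surgery to pregnancy only among women who conceived, so the timing comparison is nearly uninformative; the collected baseline scores have no stated use

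*Protocol article*

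**What the plan says.** All references are to the protocol article.

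- **Tests (Statistics).** The test follows from the type of variable: the t "test will be used for continuous variables", and "the chi-square test or Fisher’s exact test will be used for categorical variables". Non-normal data are to be described by medians, but no other test is named for them.
- **Time-to-event methods (Statistics).** "Kaplan-Meier plots will be generated for recurrence and death rates between the groups", followed by a log-rank test. Pregnancy is not mentioned.
- **Regression (Statistics).** "bivariate and multivariable logistic regression analyses will be used"; no model for a continuous outcome is named.
- **Fertility endpoints (Secondary objectives and secondary endpoints).** The list has "obstetric outcomes consisting of the time interval between the RT surgery and pregnancy" and also "the overall mean length of time during which conception was attempted". Natural pregnancy, infertility treatment, number of pregnancies and the outcome of each pregnancy are listed separately.
- **Repeated measurements (Data management).** Questionnaires, ovarian reserve, urodynamics and anorectal manometry are assessed "within 4 weeks before surgery, at 4 months postoperatively, at 12 months postoperatively, and then once a year thereafter". Table 1 also has an annual entry for pregnancy wishes and outcomes.

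**The concern.** A woman who has not conceived has no surgery-to-pregnancy interval. The article need not say that the analysis is limited to conceivers, because the definition of the variable forces it. If the surgical approach affects the chance of conceiving, the conceivers in the two arms are different kinds of women and the comparison is no longer randomised.

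Duration of attempted conception is different. It exists for every woman who tried, but for those still trying at last contact the recorded value is only a lower bound. A plain mean treats that bound as complete and is too low, more so in the arm where fewer conceive.

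Fertility is in the stated purpose of the trial, and the Discussion suggests adhesions after open surgery as a reason why it might differ. The risk is a reported finding of no difference in time to pregnancy that carries almost no information.

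The quality-of-life and function scores raise a smaller question of precision: pre-operative values are collected, but no stated method uses them.

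**Working it through.** The article gives no sample size, power or effect for fertility or quality of life, so there is no figure to reproduce. The conception rates, numbers at risk, correlations and standardised difference below are assumptions.

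**Window.** Recruitment runs from December 2018 to December 2020, and Trial status starts the primary analysis in December 2023. Follow-up is then 3 years for the last patient and 5 for the first. Windows of T = 3 and T = 5 years are used.

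**1. Mean time among conceivers.** For a constant conception rate λ:

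- share conceiving by T = 1 − exp(−λT)
- mean time among conceivers = 1/λ − T·exp(−λT)/(1 − exp(−λT))

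| T | λ per year | Share conceiving | Mean time among conceivers |
|---|---|---|---|
| 3 | 0.30 | 59.3% | 3.333 − 3(0.4066)/0.5934 = 1.28 y |
| 3 | 0.15 | 36.2% | 6.667 − 3(0.6376)/0.3624 = 1.39 y |
| 5 | 0.30 | 77.7% | 3.333 − 5(0.2231)/0.7769 = 1.90 y |
| 5 | 0.15 | 52.8% | 6.667 − 5(0.4724)/0.5276 = 2.19 y |

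The ratios are 1.388/1.278 = 1.09 and 2.190/1.897 = 1.15, against a true rate ratio of 2.

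**2. Attempt duration cut off at T.** If trying starts at time 0, the mean recorded duration is (1 − exp(−λT))/λ.

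- At 3 years: 0.5934/0.30 = 1.98 and 0.3624/0.15 = 2.42 years, a 22% difference.
- At 5 years: 0.7769/0.30 = 2.59 and 0.5276/0.15 = 3.52 years, a 36% difference.

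The uncensored means are 3.33 and 6.67 years. The distortion is smaller than for the interval, but still large.

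**3. Power over a range of conception rates.** Simulation used 1,500 runs per scenario, 60 months of follow-up, no losses and two-sided 5% tests. Five-year conception was 20% vs 35%, 30% vs 45% and 40% vs 60%. Times were either exponential or identically distributed among conceivers.

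| Women at risk per arm | t test, conceivers only | Log-rank, all women | Chi-square, conceived or not |
|---|---|---|---|
| 165 | 4% to 11% | 79% to 97% | 79% to 96% |
| 83 | 5% to 8% | 50% to 75% | 51% to 74% |

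With exponential times and 165 per arm, mean time among conceivers differed by only 0.9, 1.2 and 1.9 months in the three scenarios. With identical timing among conceivers, the t test rejects at about its nominal 5%, although conception differs by 15 to 20 percentage points.

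**4. Baseline adjustment.** With follow-up variance 1 and baseline correlation ρ, the variance is 1 for a follow-up-score t test, 2(1 − ρ) for a change-score t test and 1 − ρ² for ANCOVA. ANCOVA therefore saves ρ² against follow-up scores and 1 − (1 + ρ)/2 against change scores.

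| ρ | Saving vs follow-up score | Saving vs change score |
|---|---|---|
| 0.4 | 16% | 30% |
| 0.5 | 25% | 25% |
| 0.7 | 49% | 15% |

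At ρ = 0.5, a standardised difference of 0.3 and 165 per arm, power is 78% with either t test and 88% with ANCOVA.

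**The case against.** **A reader might infer that the plan would hide a real fertility difference. The article does not support this.** Natural pregnancy and the outcome of each pregnancy are separate endpoints under the chi-square or Fisher rule. In the simulation that test had about the same power as the log-rank test. In the 3-year example (59% vs 36%), its power is about 85% with 83 women per arm and 99% with 165. What is lost is a valid comparison of timing. The close agreement of the two tests does, however, rest on equal and complete follow-up. The plan has follow-up of unequal length and allows for 20% loss, which a chi-square test cannot take into account.

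**A reader might also infer that the baseline scores are discarded. The text does not say so.** A t test on change from baseline fits the stated rule, and the choice of model for secondary scales is often left to a statistical analysis plan, which is not shown. It can be said only that no use of the baseline is stated. The issue is precision, not bias.

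**The Kaplan-Meier sentence is not exclusive.** It names recurrence and death without ruling out other outcomes. That is correct, but the t-test rule has no exception, and read as written it covers the interval.

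**The size depends on assumed rates and on the window.** This stands, so both windows and a range of rates are shown. The selection by outcome does not depend on them.

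**Urodynamics and manometry are scheduled assessments, not listed secondary endpoints.** This also stands and lowers the weight of the baseline point for them.

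**Conclusion.** The point holds for the timing outcomes. The stated rule puts the surgery-to-pregnancy interval into a t test that can include only conceivers, and it treats censored attempt durations as complete. Under assumed rates of 0.30 and 0.15 per year, a twofold difference shrinks to about 9% over 3 years and 15% over 5 years in mean time among conceivers. Across the simulated scenarios the t test had 4% to 11% power. These figures assume constant rates (or identical timing among conceivers, in half of the simulations), no losses and no competing events.

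The comparison of whether women become pregnant is not invalidated, and the primary disease-free survival analysis is unaffected. The baseline point is a secondary one about efficiency: about 25% of the variance at an assumed correlation of 0.5. Taken together this is a change that should be made, not one on which the trial's main conclusion depends.

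**What to change.** **Main change.** Except time to pregnancy from the t-test rule. Analyse time from surgery to first pregnancy in all randomised women as time-to-event, censoring at last contact and treating death, hysterectomy or other loss of fertility as competing events. Report cumulative incidence by arm. This keeps the protocol's time origin and the randomised comparison.

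**Supportive analysis.** Use the same method from the start of trying, in women recorded in Table 1 as wishing to conceive, in place of the mean attempt duration. State that this is a post-randomisation subset.

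**Baseline scores.** For the quality-of-life questionnaires, FSFI, PFIQ-7 and function measures, replace the t test with ANCOVA or a mixed model adjusted for the pre-operative value.

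**Cost.** Analysis-plan wording, modest programming and a check that the named software produces cumulative incidence with competing events. The annual case report form must hold the date trying began, and dates of pregnancy and loss of fertility must be recorded. No extra patients or visits are needed.
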